Randomization is carried out using a web-based random number generator (details of how these random numbers are generated are available on the website) [60]. A master file was created in Excel (Microsoft Corp) by author JS, which consisted of 4 different stratification groups to correspond to the number of possible combinations: no chemotherapy and no reconstruction; no chemotherapy, with reconstruction; chemotherapy, no reconstruction; and chemotherapy and reconstruction. Using the web-based number generator, each stratification group was populated with equal proportions of the randomly ordered numbers (1, 2, or 3) that corresponded to the intervention groups to which a participant could be assigned (1: OR intervention; 2: Nature Treks VR intervention, and 3: TAU). Only research personnel who randomized the participants had access to the file. Due to the nature of this study, only partial blinding was possible. Specifically, those in the TAU group received no VR intervention, but those randomized to VR control versus the VR active intervention were blinded. Participants randomized to either the active intervention or VR control group schedule a meeting date to undergo the VR intervention, approximately 2 weeks before their surgery, during their telephone call with the study coordinator. On the day of the intervention meeting, participants complete baseline questionnaires before the intervention and additional questionnaires after the intervention (detailed in the *Measures* section). Those randomized to TAU are either emailed a link to complete the baseline measures using Qualtrics software (Qualtrics International Inc) or are mailed a hard copy, depending on their preference, 2 weeks before their surgery (baseline). On the day of surgery (preoperative period), participants again complete the measures assessing PSA that had been assessed at baseline. Five days after surgery (acute postoperative period), participants will complete the PSA measures, in addition to the other initial baseline measures. Finally, all baseline measures are readministered at the 30-day postoperative follow-up. For both postoperative follow-ups, participants have the option to receive hard copies of the measures via mail (to complete within 72 hours) or a survey link to complete the measures on the web.

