#### Measures

A variety of self-report measures are administered to participants across 4 time points of this study (ie, baseline or VR visit, preoperative period, acute postoperative period, and 30-day postoperative follow-up). Baseline measures are administered approximately 2 weeks before surgery (at the VR intervention visit for the intervention groups or via mail or web-based for the TAU group). These measures include a background sociodemographic questionnaire (eg, assessing age, marital status, diagnosis, type of surgery, previous history of surgeries, and mental health diagnoses); the Preoperative Intrusive Thoughts Inventory (PITI) [61]; the Amsterdam Preoperative Anxiety Information Scale (APAIS) [62]; the NCCN Distress Thermometer (a visual analog scale; also adapted for anxiety) [63,64]; the Peritraumatic Distress Inventory [65]; the Primary Care Screen for Posttraumatic Stress Disorder Diagnostic and Statistical Manual of Mental Disorders, Fifth Edition [66]; the Brief Resilient Coping Scale (BRCS) [67]; and the Patient-Reported Outcomes Measurement Information System (PROMIS) anxiety [68], depression [68], global health [69], fatigue [70], and emotional support scales [71]. The sociodemographic data collected were informed by the methodology used in a previous study by Grocott et al [72] that itself informed the current methodological approach. All mental health symptom scales are empirically validated self-report measures in various health populations, languages, and cultures. During the VR simulation, we also monitor participants’ skin conductance (using eSense Skin Response [Mindfield Biosystems Ltd]) and heart rate (using a Fitbit device [Google LLC]) while engaged in the VR simulation; participants are asked to report their level of distress and anxiety (using the NCCN Distress and Anxiety Thermometer scale ranging from 0 to 10) during the intervention (approximately 7 min from the start time). Throughout the simulation, research personnel complete a standardized behavioral observation form recording any notable verbal or nonverbal indications while in the intervention. After the simulation, the intervention groups complete the Igroup Presence Questionnaire [73] and a patient acceptability questionnaire (developed by the research team and including both closed-ended and open-ended items for participants to describe their impressions of the intervention). The patient acceptability questionnaire contains questions pertaining to rating the extent (on a scale ranging from 0% to 100%) to which the participant agrees to 13 statements about the VR intervention (eg, “I found the VR intervention was helpful” and “The VR intervention worsened my anxiety/concerns about my surgery”), open-ended and closed-ended questions about motion sickness, open-ended questions about what the participant liked and disliked and what they found helpful about the VR (if applicable), open-ended and closed-ended questions about whether the VR intervention was worthwhile, and a closed-ended question about other elements that should be included in the VR OR simulation.

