
On the day of surgery, all participants are asked to complete the PITI, the APAIS, and the NCCN Distress and Anxiety Thermometer either while they are in the waiting room or in the preoperative holding area (depending on when is most convenient and the timings of surgeries). Furthermore, we again monitor participants’ skin conductance and heart rate at this time. Participants are also asked to provide an additional rating for the NCCN Distress or Anxiety Thermometer while in the OR; instead of using the paper copy in the OR, the study coordinator or anesthesiologist asks participants to verbally indicate their current level of distress and anxiety (ie, on a scale ranging from 0 to 10). Five days after surgery, participants are asked to complete the NCCN Distress and Anxiety Thermometers; the PROMIS anxiety, depression, global health, fatigue, and pain intensity scales; a visual analog anxiety and distress graph; a postoperative summary form (to capture length of hospital stay and impressions of the various preoperative anxiety and distress measures); the BRCS; and the Peritraumatic Distress Inventory. Those in the active intervention group also receive open-ended questions requesting feedback to inform modifications that should be made to the second model of the simulation (in phase 3). Finally, 30 days after surgery, participants are asked to complete the NCCN Distress and Anxiety Thermometers; the PROMIS anxiety, depression, global health, fatigue, and pain intensity scales; the BRCS; and the Primary Care Screen for Posttraumatic Stress Disorder Diagnostic and Statistical Manual of Mental Disorders, Fifth Edition.

As will be detailed in the feasibility manuscript, although a number of self-report and objective measurements were obtained, the primary measures relate to feasibility (eg, recruitment and dropout rate as well as VR impressions and feedback). This feasibility study will also evaluate the extent to which these measures are completed as instructed and best represent PSA and whether preliminary trends support decreases in PSA across the study duration. The primary outcome measure for the larger future clinical trial will be determined based on this study. The proposed primary outcome measures of interest include the PITI, the APAIS, and the NCCN Distress and Anxiety Thermometers.

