#### Data Analysis

Quantitative data will first be analyzed descriptively: the recruitment, engagement, and attrition rates will be calculated; sample characteristics will be summarized (both across the total sample and within each group); and mean scores on measures will be reported (within each group). The assessment of acceptability will be based on open-ended qualitative feedback regarding impressions of the VR intervention, which will be analyzed using content analysis with NVivo 12 (Lumivero), which was designed to assist with qualitative data organization. We will also determine acceptability based on the developed Likert scale questions. Means or medians will be reported depending on the distribution of the data. A triangulation approach will be used to amalgamate data sources and comprehensively assess acceptability. Paired samples *t* tests (1-tailed) and repeated measures ANOVAs will assess whether there are changes in participant-reported symptoms across the duration of the study within the active intervention group. If power permits, independent samples *t* tests (or an ANOVA, followed by post hoc pairwise comparisons) will assess whether there are mean differences in PSA scores between (1) the active and control intervention groups and (2) the active intervention group and TAU (this will be examined descriptively if underpowered). We will also examine changes in physiological arousal (an objective indicator of distress), assessed via skin conductance and heart rate, between and within (ie, during VR intervention vs within OR) intervention groups, and we will assess whether self-reported distress and anxiety scores are correlated with the indices of physiological arousal. Physiological data will also be integrated in the VR technological paper (in development) to understand whether physiological indices change during the VR experience (indicative of immersion). Finally, if power permits, independent samples *t* tests and ANOVAs will assess whether there are mean differences in patient-reported symptoms according to certain sample characteristics (eg, age, clinically significant anxiety, history of previous surgery, and type of surgery), both within the active intervention group and within the complete sample.

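### The VR-versus-TAU comparison of PSA scores leaves out the same-scale baseline already collected; add a baseline-adjusted estimate beside the unadjusted one

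*Protocol article*

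**What the plan says.** The Data Analysis section of the protocol article names the between-arm method: independent samples t "tests (or an ANOVA, followed by post hoc pairwise comparisons) will assess whether there are mean differences in PSA scores between" the active and control VR groups, and between "the active intervention group and TAU (this will be examined descriptively if underpowered"). The comparison is made only if power allows. No baseline score, change score or stratification factor enters it, and no time point is given for the PSA scores. The paired t tests and repeated measures ANOVAs in the same section concern "changes in participant-reported symptoms across the duration of the study within the active intervention group", so they do not provide a baseline-adjusted contrast between arms.

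The baseline data exist. According to Measures, baseline takes place about two weeks before surgery, at the VR visit in the VR arms and by mail or web in TAU, and the list includes the PITI, the APAIS and the NCCN thermometer, also adapted for anxiety. The same section states: "On the day of surgery, all participants are asked to complete the PITI, the APAIS, and the NCCN Distress and Anxiety Thermometer". The Protocol section confirms that on that day "participants again complete the measures assessing PSA that had been assessed at baseline", and that in the VR groups "participants complete baseline questionnaires before the intervention and additional questionnaires after the intervention". Measures adds: "The proposed primary outcome measures of interest include the PITI, the APAIS, and the NCCN Distress and Anxiety Thermometers".

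**The concern.** After the VR control arm was dropped (Results), VR versus TAU is the only randomised contrast left for PSA scores. Limitations calls the sample underpowered, and Data Analysis makes the comparison depend on power, so the efficiency of the method matters.

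An unadjusted comparison of day-of-surgery scores treats as noise the variation between participants that their own baseline score could explain. Part of any chance difference in baseline anxiety, about r times it, also carries into the arm difference. In a sample of 23 to 30 such differences can be sizeable. At stake is the width of the interval around the preliminary utility estimate. The residual SD and the pooled baseline to day-of-surgery correlation, both useful when designing the next trial, are not outputs of the planned test.

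**Working it through.** **Inputs from the protocol article.** The target is 45 participants in three arms, so 45/3 = 15 per arm, as stated. There is no power calculation to reproduce: the sample size rests on feasibility guidelines, with no alpha, effect size or SD. Limitations gives 8 + 15 = 23 recruited by September 2023, without arm counts; Results says recruitment ended in December 2023.

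**Assumptions.** A 12 versus 11 split of the 23; 15 versus 15 as the original target per arm; r varied, because the documents do not give it; equal SDs, with results in SD units.

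**Formulas**, with N the total in the two arms:
- Unadjusted: SE = √(1/n₁ + 1/n₂); half-width = t(0.975, N − 2) × SE.
- ANCOVA on one baseline score: SE_adj = SE × √[(1 − r²)(N − 3)/(N − 4)]; half-width = t(0.975, N − 3) × SE_adj. The factor (N − 3)/(N − 4) is the small-sample cost of estimating one slope.

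**12 versus 11.** SE = √(1/12 + 1/11) = 0.417, and 2.080 × 0.417 = 0.87 SD. At r = 0.5, SE_adj = 0.417 × √(0.75 × 20/19) = 0.371, and 2.086 × 0.371 = 0.77 SD.

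**15 versus 15.** SE = √(2/15) = 0.365, and 2.048 × 0.365 = 0.75 SD. At r = 0.5, SE_adj = 0.365 × √(0.75 × 27/26) = 0.322, and 2.052 × 0.322 = 0.66 SD.

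| 95% CI half-width (SD) | 12 vs 11 | 15 vs 15 |
|---|---|---|
| Unadjusted | 0.87 | 0.75 |
| Adjusted, r = 0.2 | 0.88 | 0.75 |
| Adjusted, r = 0.3 | 0.85 | 0.73 |
| Adjusted, r = 0.4 | 0.82 | 0.70 |
| Adjusted, r = 0.5 | 0.77 | 0.66 |
| Adjusted, r = 0.7 | 0.64 | 0.55 |

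**Break-even.** The variances are equal at r = √[1/(N − 3)], which is 0.22 for N = 23 and 0.19 for N = 30. At r = 0, ANCOVA costs about 5% and 4% in variance respectively.

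**Variance ratio at 15 per arm.** 0.78 at r = 0.5 and 0.53 at r = 0.7, equivalent to 15/0.78 ≈ 19 and 15/0.53 ≈ 28 per arm unadjusted. Simulation gave the same ratios.

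**Power at 15 per arm**, two-sided 5% assumed. For an assumed effect of 0.8 SD, power is 56% unadjusted, and 67% or 83% adjusted at r = 0.5 or 0.7. For 0.5 SD it is 26%, and 32% or 44%. Adjustment therefore need not lift the comparison out of the underpowered range.

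**Cost of a baseline shift by arm.** Participants are randomised during the recruitment call (Ethical Considerations, Phase 2), before baseline. Baseline is then completed at the VR visit in one arm and by mail or web in the other. If setting alone moves baseline scores by d SD in one arm, the adjusted difference is biased by about r × d. At r = 0.7 and d = 0.3 that is 0.21 SD, and simulated coverage of the nominal 95% interval falls to about 90% (12 versus 11) and 88 to 89% (15 versus 15). At r = 0.5 and d = 0.3 it is about 93% for both sizes. For r from 0.4 to 0.7, √(SE² − SE_adj²)/r is 0.33 to 0.41 SD: below that shift the adjusted estimate still has the smaller mean squared error.

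**The case against.** The strongest reply is that nothing planned here is wrong. A t test in a randomised comparison is valid, and its interval already allows for chance imbalance. A reader might infer that the planned estimate is biased, or that a baseline difference passes into it in full. The documents support neither: the loss is one of precision, and only about r times an imbalance carries over.

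The comparison may also never be run as a test. It is conditional on power, the article itself expects low power, and feasibility measures are primary. That stands and lowers the priority. It does not remove the point, because a descriptive arm difference with an interval gains from adjustment in the same way.

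The gain rests on an unknown r. The Introduction describes PSA as transient, and the two measurements lie about two weeks apart, so a low r cannot be excluded. That also stands; it is why the table includes r = 0.2 and 0.3.

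The most serious objection is that this baseline is not clean. It follows randomisation, and its setting differs by arm. The Introduction links PSA to unfamiliar environments and encounters with health professionals, so a shift by arm is plausible. Mean squared error alone does not answer this, since coverage suffers and the bias does not shrink with more participants. It follows that ANCOVA should not replace the unadjusted estimate.

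Two further inferences fail. No section says that the arm difference will set the size of the next trial; the article ties this study to recruitment method, trial duration, choice of outcome measure, and design and implementation generally. Nor is the correlation wholly unavailable: in the active arm it can be recovered from the SD of change and the two score SDs behind the paired t tests.

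Finally, an article may leave covariates to a fuller plan. Here, though, it names the between-arm test and confines the repeated-measures analyses to one arm, so the choice can be reviewed as stated.

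**Conclusion.** The point holds as a modest, low-cost gain in precision. Both arms supply the same PSA scales before exposure and on the day of surgery, and the planned between-arm comparison does not use the earlier score. At 12 versus 11 the interval would be about 6% narrower at r = 0.4, 11% at r = 0.5 and 27% at r = 0.7. It would be about 2% narrower at r = 0.3 and slightly wider at r = 0.2. These figures rest on an assumed r, an assumed split of the 23, and a baseline not shifted by its setting.

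The documents do not support reading this as an invalid analysis, or as grounds for dropping the unadjusted difference. The adjusted estimate belongs beside it, so that readers can see whether the two agree. Because utility is a preliminary secondary objective, this is an improvement worth making but not a condition for the study's main conclusions.

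**What to change.** For each PSA scale (PITI, APAIS, NCCN Distress and Anxiety Thermometers), add to Data Analysis an ANCOVA of the day-of-surgery score on arm (VR versus TAU) and the baseline score of the same scale. Report the adjusted difference with its 95% CI, including when the comparison is treated as descriptive, together with the residual SD and the baseline to day-of-surgery correlation.

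Keep the unadjusted difference with its 95% CI beside it, and report baseline means by arm. State that baseline was taken before exposure but after randomisation, at the VR visit in one arm and by mail or web in the other, and that a setting effect would bias the adjusted estimate by about r × d. A t test on change scores is not a substitute: its variance is 2(1 − r) times that of the unadjusted comparison, so it is worse whenever r is below 0.5.

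The cost is a sentence or two of text and one model per scale, with no new data. The downsides are one degree of freedom, a slight loss if r is below about 0.2, and the possible bias. The abstract says that data collection is complete and analysis is ongoing, so the addition should be recorded as made after data collection and, if possible, before arm comparisons are seen.

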### Phase 3 (Underway)

#### Focus Groups

The focus groups are being led by 4 authors (RE, KR, GSL, and JB). The first focus group consisted of individuals randomized to the VR intervention (ie, those who received the VR OR intervention before surgery) and took place over Zoom (Zoom Video Communications, Inc). A second focus group was then conducted with individuals randomized to the TAU group or the VR control group (ie, those who did not receive the VR intervention). This focus group took place in person at the HSC and commenced with each participant trialing the VR OR prototype. Due to scheduling conflicts, we held an additional focus group for TAU participants in December 2023, and an additional focus group with VR intervention participants in February 2024. It is important to note, as we discuss in the *Results* and the *Limitations* sections, that the VR control group (ie, Nature Treks VR experience) ended up being dropped due to slow recruitment; thus, we only ran the control focus groups with individuals randomized to TAU.

The focus groups commence by reviewing the purpose of the feasibility study and the VR prototype. A semistructured question guide was developed by the research team, including several open-ended questions regarding patients’ experiences with the VR prototype, whether they believe it impacted their surgical experience, and recommendations for further development. After open-ended questions are asked, more specific questions regarding feedback on potential adaptation of the prototype are explored. The focus groups are audio recorded and transcribed using Trint software (Trint Limited). Qualitative data will be analyzed using reflexive thematic analysis [74-76], examining themes identified by the authors across participants.

#### VR Refinement

On the basis of the results of phase 2 and the focus groups, additional modifications and changes are being made to the VR prototype. As part of the feasibility study, participants from phase 2 were asked about any additional elements to be included in the VR simulation. In addition, a coinvestigator meeting was held in April 2023 where preliminary results from a case series proof-of-concept study (first 7 participants of the feasibility trial) were presented. The expert coinvestigators provided additional input on modifications based on these initial case series findings. On the basis of the findings from the feasibility trial, expert input, and focus groups, a list of additional elements to be integrated into the VR will be developed (eg, artificial intelligence integration, educational component, guided relaxation strategies, and exposure to the waiting room or recovery environments). People engaging with the VR OR will also be provided with the opportunity to customize their avatar to be more representative of themselves. This means participants will be able to change the avatar’s skin color and height to enhance embodiment. Efforts will also be undertaken to improve the diversity of the VR OR staff.

On the basis of the results from the feasibility study, focus groups, and expert input consensus, we will aim to complete the final prototype by mid-2024 for testing in a future randomized clinical trial.

### Ethical Considerations

#### Phase 1

No patient participants were involved in the development of the initial VR prototype; therefore, ethics approval was not required. However, for the audio and video recording of a live anesthetic induction process at the HSC, we obtained signed patient consent (of note, we excluded any visual of the patient).

#### Phase 2

We received ethics approval from the University of Manitoba Health Research Ethics Board on June 30, 2020 (HS23957). Ethics amendments were approved in January 2021, September 2021, April 2022, and November 2022 (Multimedia Appendix 1). Participants first gave verbal consent to be contacted for research purposes after being briefly told about the study at the individual’s surgical oncology appointment or at a preoperative education class. Alternatively, if learning about the study from a poster, patients contact our research team directly (as described in the *Recruitment* section). Participants are randomized during the recruitment call if they provide verbal consent to participate. Furthermore, we obtain verbal consent over the telephone from participants in the screening period and written informed consent before their participation in the study (via mail or email). All data are stored deidentified. Participants received a $25 CAD honorarium for participating in the feasibility trial.

#### Phase 3

In June 2023, we received ethics approval to conduct the focus groups from the University of Manitoba Health Research Ethics Board (HS26054) to recruit participants from phase 2 who indicated on their consent form that they would be willing to serve as a patient partner or adviser for future development of the VR program. For those indicating *yes*, a research assistant followed up via telephone to assess continued interest in involvement. All focus group transcript data are deidentified. All focus group participants received a $20 CAD honorarium for participating in the focus groups.

